
**Figure 2 f2:**
[figure not shown]
Workflow of tongue and pulse diagnostic image acquisition in TCM. **(A)** Tongue diagnosis via the standardized tongue imager from Zhejiang Cancer Hospital. **(B)** Pulse diagnosis with the standardized pulse device from Dajing TCM, plus biological sample collection for mechanism research and biomarker discovery.

#### Follow-up schedule and procedures

2.3.3

Follow-up examinations will be conducted at 12, 24, 36, 48, and 60 months after enrollment. During each follow-up visit:

Clinical examination encompassed comprehensive history-taking (with emphasis on gastrointestinal symptoms and treatment-related complications) and thorough physical examination. Follow-up assessments utilized structured questionnaires combined with medication verification to document patients’ TCM usage over the preceding 6 months, recorded in the ‘Follow-up Medication Record Form’ For patients reporting TCM use, TCM diagnostic data collection was immediately suspended, and patients were instructed to discontinue all TCM preparations for 1 week before returning for morning fasting reassessment. This protocol enabled dual verification through baseline-versus-follow-up data comparison and post-cessation sign monitoring, allowing differentiation between treatment-induced changes and genuine pathological manifestations.Colonoscopy will be performed according to standard clinical practices to detect adenoma recurrence (**Table 2**). The timing and frequency may be adjusted based on baseline findings according to guidelines for adenoma surveillance (14, 15).Updated laboratory tests similar to baseline will be performed to monitor changes and identify potential biomarkers of adenoma recurrence or progression.TCM syndrome evaluation will be repeated to track changes in syndrome patterns and their potential association with disease progression.Risk factor assessment will be updated, including changes in lifestyle factors (smoking, alcohol consumption, diet, physical activity).Treatment information will be collected, documenting both Western medical interventions and TCM treatments.

**Table 2 T2:** Follow-up intervals after endoscopic resection of colorectal polyps or adenomas.

Initial colonoscopy findings	Colonoscopy follow-up interval (Years)
No polyps	3–5
Hyperplastic polyp in rectum or sigmoid(diameter <10 mm)	2–3
1–2 tubular adenomas (diameter < 10 mm)	1–3
3–10 tubular adenomas	1–2
≥ 1 tubular adenoma (diameter ≥ 10 mm)	1–2
≥ 1 villous adenoma	1–2
Adenoma with high-grade intraepithelial neoplasia	1–2
Serrated lesion < 10 mm without intraepithelial neoplasia	2–3
Serrated lesion > 10 mm without intraepithelial neoplasia	1–2

In cases of special circumstances such as new symptoms (hematochezia, change in bowel habits, unexplained weight loss), additional examinations including earlier colonoscopy, enhanced CT, or MRI may be performed outside the scheduled follow-up timepoints, with these events recorded in detail.

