Baseline TCM diagnostic information (tongue appearance, pulse characteristics, and symptomatic manifestations) will be collected simultaneously by trained research personnel. Collection timing will be strictly standardized to 24–48 hours post-admission and prior to colonoscopy, exclusively during morning fasting state (8-hour food restriction, 2-hour fluid restriction) to eliminate temporary interference from dietary intake or endoscopic procedures. This observational study will enroll only patients with first-time CRA detection (confirmed through comprehensive history review and colonoscopy of no previous adenoma history). At baseline, participants will receive no adenoma-specific treatments (including oral Chinese herbal medicine, herbal enemas, or other TCM interventions). During hospitalization (mean duration ≤1 week), patients will receive only routine Western medications related to surgical procedures (e.g., bowel preparation agents), ensuring baseline TCM diagnostic data accurately reflected the pathological status. Post-discharge self-administration of Chinese herbal medications is possible; this aspect will be systematically monitored during the follow-up period.

Clinical data collection will focus on comprehensive documentation of adenoma characteristics through colonoscopy and pathological examination. Colonoscopy findings will include the number, size, location, and morphological features of adenomas. Pathological assessment will document adenoma type (tubular, tubulovillous, villous), degree of dysplasia, and margin status. These parameters are essential for risk stratification of patients and determination of appropriate surveillance intervals.

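### The only stated look-back for TCM use covers half of each 12-month visit interval, and without an on-treatment measurement the claim to separate treatment effects from disease signs is not supported

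*Protocol article*

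**What the plan says.** Section 2.3.3 (Follow-up schedule and procedures) fixes the visits: "Follow-up examinations will be conducted at 12, 24, 36, 48, and 60 months after enrollment". At each visit a structured questionnaire with medication verification documents "TCM usage over the preceding 6 months" on the Follow-up Medication Record Form. The same section also has a general item on Western and TCM treatments, and Table 1 ticks TCM treatment and concomitant medications at all five follow-up visits. Neither of these states a look-back period.

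Section 2.3.2 says that participants receive no TCM treatment for adenoma at baseline. It accepts that they may take herbal medicines after discharge and promises that "this aspect will be systematically monitored during the follow-up period".

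For patients who report TCM use at a visit, section 2.3.3 says that "TCM diagnostic data collection was immediately suspended, and patients were instructed to discontinue all TCM preparations for 1 week before returning for morning fasting reassessment". It describes this as "dual verification through baseline-versus-follow-up data comparison and post-cessation sign monitoring", "allowing differentiation between treatment-induced changes and genuine pathological manifestations".

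Section 2.3.10 plans time-dependent Cox models for dynamic risk factors and regression models relating TCM syndromes to outcomes.

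**The concern.** There are two linked problems.

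First, a 6-month look-back does not fit a 12-month visit interval. A patient who took TCM only in the first half of an interval can truthfully answer that there was no use in the window, and is then recorded as a non-user. The Discussion credits a TCM formulation with fewer recurrences after resection, so on the authors' own account TCM use bears on a primary outcome. A time-dependent analysis of TCM use, or of syndrome updated at each visit, needs to know when patients were exposed. The first unrecorded stretch is the half-year directly after resection.

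Second, the article says its procedure tells treatment-induced changes apart from signs of disease. That needs some measurement taken under treatment. The procedure as described removes it: reported users are measured only after stopping. A user who does not return for the reassessment would also have no TCM data for that visit.

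**Working it through.** **Coverage of the 6-month window.** Inputs from section 2.3.3: visits at 12, 24, 36, 48 and 60 months; look-back 6 months.

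- Covered: months 6–12, 18–24, 30–36, 42–48 and 54–60. That is 5 × 6 = 30 months.
- Not covered: months 0–6, 12–18, 24–30, 36–42 and 48–54. That is 60 − 30 = 30 months.
- Share covered: 30/60 = 50%.
- With a look-back equal to the visit interval: 5 × 12 = 60 of 60 months, or 100%.

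**Chance that a course of TCM is missed entirely.** The article gives no course lengths, so the length L (in months) is an assumption, as is a start time spread uniformly over the 12-month interval. Each interval opens with a 6-month gap. A course lies wholly inside the gap only if it starts in the first 6 − L months, so the chance is (6 − L)/12 for L up to 6, and zero beyond that.

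- L = 1: 5/12 = 42%
- L = 2: 4/12 = 33%
- L = 3: 3/12 = 25%
- L = 6 or more: 0%

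A course of six months or longer always reaches a window and is detected. Its recorded duration can still be cut short if the form keeps only what falls inside the window. A course running from month 0 to month 9 would show as 9 − 6 = 3 months.

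**What is measured in reported users.**

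- Baseline: no TCM treatment for adenoma (section 2.3.2).
- Follow-up visit: sign collection suspended.
- Reassessment: after one week off all TCM preparations.

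Every value is therefore off treatment. The change from baseline to reassessment combines any lasting treatment effect with elapsed time, the resection itself and the course of disease. Nothing in the sequence isolates the treatment part within a user.

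**Who triggers the rule.** On the stated window, a patient who stopped TCM five months before the visit is a reported user and is sent for reassessment. One who stopped seven months before is handled as a non-user.

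**The case against.** The strongest reply is that the 6-month question is not the only record of TCM use. The general treatment item in section 2.3.3 and the TCM-treatment row in Table 1 apply at every visit with no 6-month limit, and might cover the full interval. The 6-month question can also be read mainly as the trigger for suspending sign collection. The form is not shown, and an article may leave its date and product fields to it. This stands in part: a reader might infer that half of all TCM exposure is lost, or that the earlier months are never asked about, and the document does not establish either. Half is the share of calendar months in the one stated window. The share of actual use missed depends on how long courses last, and long-term use is detected at every visit. The reply does not remove the mismatch, because the only period the article states fails to fit its own schedule, and any fuller record would still have to be reconciled with it.

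A reader might also infer that incomplete TCM use confounds the association between baseline syndrome and recurrence. The text does not support that. Participants are untreated at baseline, so later TCM use comes after baseline syndrome and may mediate its effect. The concern applies to analyses of TCM use itself and of time-updated syndrome.

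On the second problem, measuring everyone off treatment is a coherent choice, because it matches the baseline condition. User versus non-user comparisons and change from an untreated baseline also give some information, though confounded. To call the separation impossible would therefore go too far.

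Finally, section 2.3.7 provides for tracking missing data with reasons, multiple imputation and sensitivity analyses. That answers part of the worry about users who do not return. The article gives no non-return rate, so the extent of that loss cannot be stated.

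**Conclusion.** The point holds in this form. The only look-back the article states for TCM use covers 30 of 60 follow-up months and omits months 0–6 after resection. That does not fit the promise of systematic monitoring in section 2.3.2, or a time-dependent analysis in section 2.3.10 that uses TCM exposure or time-updated syndrome. If that form is the operative record, about 25% of 3-month courses and 42% of 1-month courses would go unseen, on the assumption of uniform start times, while courses of six months or more would be detected. The effect is to place some past users among the non-users. Its effect on any hazard ratio cannot be sized from the document.

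The differentiation claim is not supported by the procedure described, because no on-treatment measurement is planned for reported users. This should be corrected. It does not undermine the baseline syndrome analyses.

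**What to change.** - Change the recall window on the Follow-up Medication Record Form to the time since the last visit (since discharge at the first visit), with start and stop dates. Apply the same window to the general treatment item and to the TCM-treatment row of Table 1, so that there is one consistent exposure history.
- Either also collect the TCM questionnaire, tongue and pulse data from everyone at the scheduled visit, flagging current TCM use and treating any later reassessment as a second measurement, or withdraw the differentiation claim.
- Reconcile the instruction to pause TCM in section 2.3.3 with the description of the study as observational in section 2.3.2. Which clinical rule should apply is not for this review.

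The cost is a changed form field, a procedural sentence and, under the first option, one additional assessment for patients who are already at the visit. The downside is somewhat more recall error over 12 months than over 6; the medication verification already planned should help to limit it.

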### Study population

2.2

This study will recruit 15,000 newly diagnosed CRA patients across 12 hospitals in China. As a prospective, multicenter integrative Chinese-Western medicine cohort study, we will confirm CRA diagnosis through colonoscopy and pathological verification, adhering to the ‘Consensus on Pathological Diagnosis of Gastrointestinal Adenoma and Benign Epithelial Polyps’ (11) (Digestive System Group, Chinese Pathology Society). Participating medical centers encompass diverse geographic regions across eastern, central, and western China, with patient populations including referrals from external institutions to ensure broad demographic representation. Tertiary hospitals with specialized facilities were selected as research centers, possessing substantial expertise in standardized colonoscopic procedures and pathological diagnosis to guarantee diagnostic accuracy and follow-up integrity.

Inclusion criteria: (1) meeting the diagnostic criteria for CRA; (2) age ≥18 years; (3) signed informed consent.

Exclusion criteria: (1) history of malignant tumors; (2) previous radiotherapy, chemotherapy, or colorectal surgery; (3) severe cognitive impairment, dementia, or psychiatric disorders.

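### Follow-up signs are taken after a week off TCM, but baseline signs have no such interval, so the comparison of the two may be uneven for recent TCM users

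*Protocol article*

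**What the plan says.** **Follow-up** (protocol article, section 2.3.3). Participants are asked about "TCM usage over the preceding 6 months". If they report any, sign collection stops at once and "patients were instructed to discontinue all TCM preparations for 1 week before returning for morning fasting reassessment". The stated gain is "dual verification through baseline-versus-follow-up data comparison and post-cessation sign monitoring", meant to tell treatment effects from disease. The same section adds that "TCM syndrome evaluation will be repeated to track changes in syndrome patterns and their potential association with disease progression".

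**Baseline** (section 2.3.2). "Collection timing will be strictly standardized to 24–48 hours post-admission and prior to colonoscopy", in the fasting state. On treatment: "At baseline, participants will receive no adenoma-specific treatments (including oral Chinese herbal medicine, herbal enemas, or other TCM interventions"). Only routine Western drugs connected with the procedure are given in hospital. These conditions are described as "ensuring baseline TCM diagnostic data accurately reflected the pathological status".

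**Eligibility** (section 2.2). The exclusions concern earlier malignancy, earlier radiotherapy, chemotherapy or colorectal surgery, and cognitive or psychiatric disorder. None concerns recent TCM use.

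**Recording** (Table 1). TCM treatment and concomitant medications are both ticked at baseline and at every follow-up visit.

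**The concern.** Both time points share an aim: signs that show the patient's condition rather than a recent remedy. At follow-up the plan secures this with a stated interval off every TCM preparation. At baseline it relies on the absence of adenoma-specific treatment and on the drug rule in hospital. Neither reaches back before admission, and neither clearly covers TCM taken for some other complaint. Baseline use is recorded, yet the article attaches no action to the record, whereas the same information at follow-up triggers suspension and a week's break.

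At stake is the comparison of baseline with follow-up signs. Section 2.3.3 uses it as one of its two checks on treatment effects, and also relates change in syndrome to progression. For someone using TCM until admission, part of an apparent change in tongue, pulse or syndrome could come from the different time off TCM at the two measurements.

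**Working it through.** The plan states no figure to reproduce. The check sets its two timing rules against each other.

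**Inputs**
- Time off TCM at follow-up for a reported user: 1 week = 7 days (section 2.3.3).
- Time of baseline signs: 24 to 48 hours after admission = 1 to 2 days (section 2.3.2).
- TCM during the stay: none, because only routine Western drugs are given (section 2.3.2).
- Days from last TCM intake to admission, *a*: not given in the article, so it is varied below.

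**Step 1: follow-up.** A participant either reports no TCM in the preceding 6 months or has stopped for a week. With accurate reporting and compliance, all follow-up signs are taken at least 7 days after last intake.

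**Step 2: baseline.** Time off TCM = *a* + 1 (signs at 24 h) to *a* + 2 (signs at 48 h) days.

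**Step 3: shortfall against 7 days.** It runs from max(0, 7 − (*a* + 2)) = max(0, 5 − *a*) to max(0, 7 − (*a* + 1)) = max(0, 6 − *a*).

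| Last intake before admission, *a* (days) | Time off at baseline (days) | Shortfall (days) |
|---|---|---|
| 0 | 1–2 | 5–6 |
| 1 | 2–3 | 4–5 |
| 2 | 3–4 | 3–4 |
| 3 | 4–5 | 2–3 |
| 4 | 5–6 | 1–2 |
| 5 | 6–7 | 0–1 |
| 6 or more | 7 or more | 0 |

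The mismatch therefore exists only if the last intake was less than 5 days before admission (signs at 48 h) or less than 6 days (signs at 24 h). People who never use TCM, or start only after discharge, are unaffected.

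**Step 4: would a baseline washout be workable?** Started at admission, a 1-week break puts signs at day 7, which is 7 − 2 = 5 to 7 − 1 = 6 days later than the 24 to 48 hour rule allows. It would also use up the whole 7-day baseline window in Table 1. A washout is therefore not a good remedy.

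**The case against.** The strongest reply has four parts.

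*The different rules have a reason.* Only first-time adenoma patients without adenoma treatment are enrolled, and section 2.3.2 expects herbal self-medication after discharge. The week off answers that expected exposure, and an outpatient can be sent away and called back in a way that an inpatient awaiting colonoscopy cannot. This stands as an argument against a baseline washout. It does not make the two measurements comparable for someone who was already taking TCM for another complaint.

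*The article is condensed.* Handling of recent TCM use may sit in the operating procedures, the forms or the analysis plan. This stands for the date of last intake, which the forms may already hold. But the point does not rest on silence alone: applying both published rules as written can set signs after a week off against signs after a day or two off.

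*Baseline use is already captured.* Correct: two rows of Table 1 do so, and neither is limited to adenoma treatment. A reader might infer that the plan fails to ask about TCM at baseline; Table 1 shows otherwise. What the article lacks is any consequence of the answer.

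*The affected group is hypothetical.* The article gives no rate of TCM use before admission. If the baseline treatment rule is read as barring every kind of TCM, the group shrinks, although that rule still names no period before admission. The table above counts days, not bias. This stands in full and limits the weight of the point.

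**Conclusion.** The point holds, with modest weight. Follow-up signs from reported users come at least 7 days after last intake. Baseline signs may come after as little as 1 to 2 days, a difference of up to 5 to 6 days. This minimum is inferred from the timing rules; the article does not state it. It assumes TCM taken until admission for a reason other than the adenoma and stopped on admission.

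A reader might go further and infer that baseline signs are generally contaminated, or that the study's results are biased. The article does not support either. It gives neither the number of such participants nor any evidence on how signs differ between 1 to 2 and 7 days off TCM, so the size and direction of any effect are unknown. The week's break shows only that the plan regards recent TCM as a possible influence on signs. The second check, monitoring signs after stopping, does not depend on baseline. Both primary outcomes, adenoma recurrence and colorectal cancer, are confirmed histologically (section 2.3.5), so their ascertainment is unaffected. What remains is a possible unevenness in analyses of change in TCM signs, for a subset of unknown size.

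**What to change.** Keep the 24 to 48 hour rule and add no washout at baseline. Instead:

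1. Add the date of last TCM intake, for any preparation and any indication, to the existing baseline TCM-treatment record, if the forms do not already hold it.
2. Flag baseline signs taken less than 7 days after that date.
3. Repeat the analyses of change in syndrome, tongue and pulse without the flagged records, or adjusted for time off TCM, and report the result beside the main one.

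This does not make the two collection rules identical. It makes the difference visible and lets its influence be examined. The cost is one date field and one sensitivity analysis, which will use fewer participants if flagged records are left out. Visit schedule, sample size and primary outcomes stay as they are. The date is best recorded at the baseline interview, since recall of it later would be less reliable.

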TCM syndrome questionnaires focusing on major symptoms (abnormal stool characteristics, altered bowel habits, abdominal pain, abdominal distension) and minor symptoms (gastric discomfort, fatigue, fever, chills, headache).The TCM Constitution Questionnaire was developed by [name] from Beijing University of Chinese Medicine.Tongue diagnosis using standardized tongue imaging equipment developed by Zhejiang Cancer Hospital (**Figure 2A**). Equipped with a 60-megapixel Leica lens and D65 standard light source, this device ensures accurate tongue color reproduction. Participants were required to fast and abstain from water for 4 hours before data collection to avoid interference with tongue coating color. During imaging, participants sat upright in a quiet environment, extended their tongues naturally, and remained relaxed to minimize tongue deformation. Images were captured only after confirming no obstruction of the tongue, with requirements to fully display both the tongue body and coating. RGB values were recorded, using RGB (255, 224, 189) as the reference standard. Subsequent image processing involved standardization of RGB and HSV channels to ensure color consistency, and a stable algorithm was applied to improve the accuracy of tongue diagnosis.Perform pulse diagnosis using the standardized pulse diagnostic device developed by Dajing Traditional Chinese Medicine (**Figure 2B**). This device is fitted with high-sensitivity pressure sensors, which accurately contact the “Cun”, “Guan”, and “Chi” pulse positions on the wrist for data acquisition. Prior to measurement, participants fasted and refrained from water for 4 hours, maintained physical relaxation, and ensured correct wrist positioning. After the examiner confirmed the pulse points, participants placed their forearms on the device. The instrument automatically collected pulse waveforms and key parameters to ensure data reproducibility. Pulse data were uploaded to an analysis system, where an intelligent algorithm generated pulse diagnosis results. Key pulse waveform parameters included pulse amplitude and cycle, with output results classifying pulse patterns such as “Chen” (deep), “Shuo” (rapid), “Xu” (deficient), “Shi” (excessive), and "Chi"(slow).Blood samples: 6-8ml of whole blood was collected using EDTA anticoagulant tubes, processed within 4 hours to separate plasma, and stored at -80 °C.Tongue coating samples: collected using sterile swabs from patients in a fasting state before tooth brushing.Stool samples: collected fecal swabs before patient endoscopic treatment.Saliva samples: 5ml or more, collected after patients abstain from food, water, and oral hygiene for 1 hour.Adenoma tissue: collected during endoscopic procedures, with paired normal mucosa when possible.

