#### Outcomes

2.3.5

The primary outcomes of this prospective multicenter cohort study comprise two main endpoints: CRC occurence and CRA recurrence is defined as any histologically confirmed CRA detected during scheduled follow-up colonoscopy examinations at 12, 24, 36, 48, and 60 months after baseline. Each adenoma will be systematically evaluated according to standardized criteria, including anatomical location within the colorectum, maximum diameter measured by open biopsy forceps, and total number of lesions. Histological classification will follow the World Health Organization criteria.

For CRC occurence, the outcome is defined as any histologically confirmed CRC diagnosed during the follow-up period. Each case will undergo comprehensive assessment including TNM staging classification according to the American Joint Committee on Cancer (AJCC) 8th edition, detailed histological type and grade evaluation, and precise documentation of tumor location and size. To ensure data quality and consistency, all colonoscopy procedures will be performed by certified endoscopists following standardized protocols, and all pathological specimens will undergo centralized review by experienced gastrointestinal pathologists.

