For continuous variables following normal distribution, independent sample t-tests will be used to compare differences between groups. For categorical variables, chi-square tests or Fisher’s exact tests will be applied as appropriate. Multivariate analysis will incorporate instrumental variables, multiple linear models, logistic regression (20), and Cox regression to explore the relationship between TCM syndromes and patient outcomes (21).

An interim analysis will be conducted when 50% of the target sample size is achieved. All statistical tests will be two-sided, with P<0.05 considered statistically significant.

Beyond determining the total sample size, we further considered the statistical power for key subgroup analyses. Based on prior literature reviews (22), the expected distribution of major TCM syndrome types in the study population is as follows: the “Dampness-Heat Accumulation” syndrome (dominant type) accounts for 28.70%, while the “Spleen Deficiency with Dampness Retention” and “Spleen Qi Deficiency” syndromes (major subgroups) account for 9.18% and 8.06%, respectively. With a total sample size of 15,000 participants, approximately 4,305 cases are expected to be classified under “Dampness-Heat Accumulation,” 1,377 under “Spleen Deficiency with Dampness Retention,” and 1,212 under “Spleen Qi Deficiency.” This sample allocation accurately matches the anticipated syndrome distribution, enabling the investigation of outcomes such as adenoma recurrence and malignant transformation, and fully meets the statistical requirements for comparative analyses among different TCM syndrome types.

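### Recurrence counts only at scheduled colonoscopies, while a symptom shared with the TCM syndrome questionnaire can prompt unscheduled ones, so syndrome–recurrence estimates may be biased in a direction set by the counting rule

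*Protocol article*

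**What the plan says.** Four statements in the protocol article bear on this.

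- **Trigger (2.3.3, Follow-up schedule and procedures).** In circumstances "such as new symptoms (hematochezia, change in bowel habits, unexplained weight loss), additional examinations including earlier colonoscopy" is allowed. Such examinations "may be performed outside the scheduled follow-up timepoints, with these events recorded in detail".
- **Exposure (2.3.2, Baseline and follow-up data collection).** The syndrome questionnaire covers "major symptoms (abnormal stool characteristics, altered bowel habits, abdominal pain, abdominal distension", among other items. Section 2.3.3 adds: "TCM syndrome evaluation will be repeated to track changes in syndrome patterns and their potential association with disease progression".
- **Endpoint (2.3.5, Outcomes).** Adenoma recurrence is histologically confirmed adenoma "detected during scheduled follow-up colonoscopy examinations at 12, 24, 36, 48, and 60 months after baseline". Colorectal cancer has no such limit: "any histologically confirmed CRC diagnosed during the follow-up period".
- **Analysis (2.3.10, Statistical analysis).** Logistic and Cox regression, among others, are planned "to explore the relationship between TCM syndromes and patient outcomes", with time-dependent Cox models for factors that change.

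Table 1 shows colonoscopy at each yearly visit. Section 2.3.3 lets timing follow baseline findings, and Table 2 gives intervals of 1–3 years for one or two small tubular adenomas and 1–2 years for higher-risk adenomas.

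**The concern.** A new change in bowel habit can do two things at once: alter the recorded syndrome and bring forward a colonoscopy. How closely participants are examined may then depend on the exposure under study. Adjusting for baseline adenoma features does not remove a dependence that arises during follow-up.

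Under the endpoint as worded, an adenoma found and removed at a symptom-triggered examination is not a recurrence, and it is no longer there at the next scheduled colonoscopy. The participant returns to risk with a clean colon and no event. A syndrome with more such examinations therefore records fewer recurrences. If the finds are counted instead, the same syndrome has its adenomas seen sooner, and with long scheduled intervals it accrues more events within five years.

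Relating syndromes to prognosis is a central aim, and a larger sample does not shrink a bias of this kind.

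**Working it through.** **The plan's figures.** The point disputes none of them. The recurrence sample size reproduces: (1.96 + 1.28)² × 0.58 × 0.42 / 0.02² = 6,393.04, rounded up to 6,394; 6,394 / 0.8 = 7,993 after rounding up.

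**Inputs from the article.** Five-year recurrence 58%; 15,000 enrolled; 20% loss; Dampness-Heat Accumulation 28.70%; colonoscopy intervals of 1 to 3 years.

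**Assumptions not in the documents.** Constant onset hazard; every adenoma present is seen and removed; the scheduled dates do not move after an unscheduled examination; unscheduled examinations occur at random at rate u, with u = 0.05 per year in the comparison group and 0.10, 0.20 or 0.30 in the symptomatic syndrome. The true syndrome effect is nil.

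**Step 1, hazard.** h = −ln(0.42)/5 = 0.1735 per year.

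**Step 2, endpoint as worded.** The probability that an adenoma is present at a scheduled examination t years after the last clean scheduled one is p = h/(h+u) × (1 − exp(−(h+u)t)).

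- *Annual, t = 1.* u = 0.05: p = 0.1555. u = 0.20: p = 0.1448. Each interval is one year, so p is also the yearly event rate. Ratio 0.1448/0.1555 = 0.93.
- *Years 2 and 4, t = 2.* p = 0.2798 and 0.2444. Events 1 − (1−p)² = 0.4813 and 0.4291. Person-years 2p + 4p(1−p) + 5(1−p)² = 3.959 and 4.082. Rates 0.1216 and 0.1051, ratio 0.86.
- *Year 3 only, t = 3.* p = 0.3793 and 0.3130. Person-years 3p + 5(1−p) = 4.241 and 4.374. Rates 0.0894 and 0.0716, ratio 0.80.

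**Step 3, all finds counted.** The event time is the first examination of any kind after onset. For the single 3-year schedule, the event probability is 1 − exp(−3h) plus the integral from 3 to 5 of h·exp(−ht)·(1 − exp(−u(5−t))) dt. This gives 0.4147 and 0.4381. Integrating the time to first find or year 5 gives 4.149 and 4.047 person-years. Rates 0.0999 and 0.1083, ratio 1.08. The other schedules follow in the same way.

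| Null rate ratio, rate versus 0.05 per year | Annual | Years 2, 4 | Year 3 only |
|---|---|---|---|
| As worded, 0.10 | 0.98 | 0.95 | 0.93 |
| As worded, 0.20 | 0.93 | 0.86 | 0.80 |
| As worded, 0.30 | 0.89 | 0.79 | 0.70 |
| All counted, 0.10 | 1.00 | 1.01 | 1.03 |
| All counted, 0.20 | 1.00 | 1.02 | 1.08 |
| All counted, 0.30 | 1.01 | 1.04 | 1.13 |

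Simulation of the same set-up agrees to within about 0.01 (for example 0.87 for the 2-yearly schedule as worded, and 1.03 and 1.07 when all finds count, at 0.20).

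**Step 4, would it show?** For illustration, treat Dampness-Heat as the symptomatic syndrome: 15,000 × 0.287 × 0.8 = 3,444 retained, against 12,000 − 3,444 = 8,556.

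- *Annual, 0.20 versus 0.05.* Events 0.5425 × 3,444 = 1,868 and 0.5704 × 8,556 = 4,880; z = ln(0.931)/√(1/1,868 + 1/4,880) = −0.0713/0.0272 = −2.6.
- *Annual, 0.10 versus 0.05.* Events 0.5610 × 3,444 = 1,932; z = ln(0.976)/√(1/1,932 + 1/4,880) = −0.9. Simulation gave a ratio of about 0.97 and z of about −1.0.

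**Step 5, Cox scale.** A simulation with 0.15–0.35 versus 0.05 per year and sensitivity of 1.0 or 0.8 gave null hazard ratios as worded of 0.86–0.96 (annual), 0.76–0.92 (2-yearly) and 0.69–0.90 (3-yearly). With all finds counted they were 1.01–1.03, 1.04–1.13 and 1.09–1.37. With equal unscheduled rates every value was 0.99–1.01, which isolates the mechanism. At sensitivity 0.8 with a single 3-year examination, the upward bias was about as large as the downward one.

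**Step 6, does a better model remove it?** If all finds count, the chance of a positive examination d years after the last is 1 − exp(−hd). Its complementary log-log is log h + log d, so log d enters as an offset. Fitted to simulated data (600,000 per group), the syndrome ratio was 0.99–1.01 for every schedule and rate in the table.

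**The case against.** Several stronger readings are tempting, and the documents do not support them.

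- *Ascertainment of recurrence rises with the exposure.* Examinations may rise, but section 2.3.5 keeps unscheduled finds out of the recurrence endpoint, so counted events fall.
- *The estimates are biased for certain, and a false positive follows.* Bias needs unscheduled rates that differ by syndrome. The article gives none, and the examination is discretionary. At 0.10 versus 0.05 with annual colonoscopy nothing would reach significance.
- *Any syndrome with bowel symptoms is affected.* The trigger is a new symptom. A long-standing complaint that shaped the baseline syndrome does not meet it, so the link is strongest for time-updated syndrome. The article also ties altered bowel habits to no particular syndrome: it is one of several questionnaire items, beside tongue and pulse findings. Using Dampness-Heat in step 4 is illustrative only.
- *Cancer is affected in the same way.* Cancer counts whenever it is diagnosed, and an earlier colonoscopy mainly brings the diagnosis forward. With 0.35% of 12,000 there would be about 42 cancers, too few for a small shift to matter.

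It is also fair to say that covariates for examination history may sit in an analysis plan that is not shown, and that unscheduled events are already recorded. What remains is the recurrence definition, which the article states and which such a plan would inherit.

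**Conclusion.** The point stands in conditional form. The overlap between trigger and questionnaire item is in the text, and so is the scheduled-only recurrence definition. If unscheduled examination rates differ by syndrome, the definition as worded pulls null syndrome ratios below 1: 0.93 to 0.80 at 0.20 versus 0.05 per year, and only 0.98 at 0.10 versus 0.05 with annual colonoscopy. Counting every find in an ordinary model leaves almost no bias with annual examinations and an upward one with longer intervals, 1.02 to 1.08 at the same rates. These sizes rest on assumed rates, complete detection and fixed scheduled dates, so they show direction and order of magnitude and are not a forecast. The matter deserves correction because the syndrome comparison is central and the remedy is cheap. No claim is made about cancer.

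**What to change.** 1. Define adenoma recurrence as any histologically confirmed adenoma at any follow-up colonoscopy, scheduled or not.
2. For the syndrome analyses, use an interval-censored model, or a per-examination complementary log-log model with log time since the last colonoscopy as offset.
3. Show the scheduled-only definition as a sensitivity analysis.
4. Report colonoscopies per person-year and their indication by syndrome, from the events that section 2.3.3 already has recorded.

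Do not adjust for indication or censor at symptom-triggered examinations in the main model. Indication is partly the exposure itself and may be caused by the adenoma, and such censoring may be informative. The proposed model has a limit of its own: it takes examination timing as unrelated to the presence of an adenoma, given syndrome. That is a reason to show both definitions side by side.

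The cost is a reworded endpoint, a revised analysis paragraph, some extra analysis work and slightly wider intervals. It needs no additional patients or procedures, and no change to when colonoscopies are done.
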